#### Selection of foods for promotion

Promoted items included a combination of fruits, vegetables, low-fat snacks, lower calorie beverages, and whole grain products. The items were intended to serve as healthy alternatives for items most frequently purchased from corner stores, including nutrient-poor, calorie-dense snack foods and drinks (i.e., chips, cookies, sodas) and staple food items (i.e., bread, cereal, milk, cheese). Promoted foods fell into one or more categories as defined by the U.S. Food and Drug Administration (FDA) [37]:Low-fat – 3 g or less per Reference Amount Customarily Consumed (RACC) or 100 g and not more than 30% of calories from fatReduced fat – at least 25% less fat per RACC or 100 gReduced sugar – at least 25% less sugar per RACC or 100 gLow-calorie – 40 calories or less per RACC or 120 kcal or less per 100 gReduced calorie – at least 25% fewer calories per RACC or 100 gHigh-fiber – contains 20% or more of the Daily Value for fiber per RACC.

The intervention consisted of three phases, each of which expanded upon the preceding phase, so that by the final phase, all foods and beverages were promoted simultaneously. Phase 1, from February to April 2013, promoted lower calorie/fat beverages including 1% milk, bottled water, and selected reduced calorie colas. Phase 2, from April to June 2013, promoted nutrient-dense staple foods including 100% whole wheat bread, canned tuna in water, and frozen vegetables, in addition to Phase 1 drinks. Phase 3, from June to August 2013, promoted lower fat snack foods; including fresh fruit, low fat granola bars, and baked potato chips, in addition to Phase 1 & 2 foods.

#### Pricing intervention

A previous Baltimore-based corner-store study described the importance of addressing both financial risk of stocking new products and the psychosocial burden that many storeowners feel in response to the pressure of stocking promoted foods [38]. BHRR was designed to reduce this burden by allowing storeowners to purchase healthier promoted items at reduced costs from the participating wholesaler. The amount of discount applied to each promoted item was determined through formative research with wholesale staff (as the minimum discount required to result in increased sales), and with storeowners (as the minimum discount required by retailers to agree to stock the foods and pass through savings to customers (known as channel or retail pass-through). Discounts ranged from 10-30% and were similar to amounts applied in previous studies [20,22,39]. Discounts on promoted items were automatically applied at wholesale registers to stores receiving the pricing intervention (n = 12) from February to August 2013. Grant funding was used to reimburse the wholesalers. In exchange for discounts, the pricing group storeowners (Groups 1 & 3) agreed to the terms of the performance allowance: to stock the promoted foods, to provide retail pass-through to customers, and to display communications materials (combined group only). Storeowner compliance to the performance allowance strategy was monitored throughout the program through process evaluation. Item discounts were introduced at each phase and sustained for the duration of the program so that during the first month only beverages were discounted, and by the last month, all promoted foods were discounted simultaneously.

#### Communications intervention

##### Wholesaler-level

The communications portion at the wholesaler-level was minimal due to the necessity to prevent cross-contamination of store owners in the pricing and control groups (Groups 1 & 4). ‘Hidden’ communications for Groups 2 & 3 (Communications & Combined groups) included 1) marking promoted foods and beverages with a 2′ circumference BHRR logo sticker at both Cash & Carry locations, and 2) providing intervention store owners with a pamphlet that contained exact aisle locations for the items. Wholesale staff members were instructed to keep the promoted items stocked at all times during the intervention period.

##### Store-level

A graphic artist and research staff developed store-level communications materials based on formative research findings. Preferred words and phrases cited by corner store customers included ‘energy’, ‘living better’, ‘clean and fresh’, ‘natural’, ‘fresh foods at a reasonable price’, and ‘100%’ (as in whole grains). Other suggestions for point of purchase materials were to provide quick descriptive words that explained why a particular food was healthy (i.e., fiber-rich, heart-healthy), as well as quick, catchy sayings (i.e., ‘refresh!’, ‘power up!’) to appeal to consumers. Posters and window signs were requested to be ‘simple’ and ‘easy to read’ since the amount of time customers spent in the store was brief. The colors purple and orange were used in all communications materials and were selected to match Baltimore City professional football and baseball teams. Materials were piloted in the community and revised before intervention implementation to ensure acceptability and resonance.

For the communications stores (Groups 2 & 3), each phase included 4–5 visits to stores for interactive sessions that included giveaways, educational handouts or recipe cards, and taste tests or educational activities. Promotional materials were tailored to each phase’s theme. For example, in-store promotions for Phase 1: Beverages, included blind taste testing of lower calorie beverages, an educational display showing the amount of sugar in commonly consumed drinks, and free drink tumblers with the project logo. Posters displayed the benefits of switching to water or a low-calorie drink, and shelf labels and talkers highlighted promoted items on the shelves. The communications stores also received a small refrigerator or freezer to store fresh or frozen fruits and vegetables and other healthy foods as an additional incentive.

#### Interventionist training

A BHRR manual of procedures was developed and used to train interventionists and to standardize practice across field sites. A 2-day interventionists’ training, led by the study coordinator, included nutrition education sessions, demonstrations and role-play, prior to intervention implementation. Weekly staff meetings served to address issues associated with program implementation.

#### Data collector training

Before beginning the study, data collectors completed a computer-based course in the protection of human research subjects (CITI Program, University of Miami). Each data collector also participated in a 2-day, in-person, data collector training program led by the Principal Investigator, which reviewed: 1) human subjects ethics principles and procedures, 2) recruitment, sampling and consenting procedures, and 3) instruments and protocol for delivery. Data collectors were trained using a combination of lectures, role-play, and supervised practice interviews.

### Outcomes and measures

Outcomes were assessed at a minimum of two time points. Baseline interviews were conducted with small storeowners and consumers from April to December 2012. Post-intervention interviews were conducted from November 2013 to March 2014. All interviews were conducted in a quiet setting in or near corner stores, in participants’ homes, or at the Johns Hopkins Bloomberg School of Public Health. Interviews with storeowners whose primary language was Korean were conducted by Korean-speaking research staff. English versions of forms were used for all data collection. A summary of study measures is shown in Table 2.

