## Methods

### Study design

BHRR is a 2x2 factorial RCT (Figure 1). Twenty-four small corner stores located in low-income census tracts of Baltimore City were randomized to one of four treatment groups: communications only (n = 6), pricing only (n = 6), combined communications and pricing (n = 6), or control (n = 6). Performance allowances in the form of healthy food discounts (10-30% off wholesale price) were directed from the wholesaler to the pricing only and combined intervention stores (12 stores total) at checkout for 6 months. In return for the discounts, storeowners were asked to stock selected healthier foods, and display communications materials and/or pass discounts to their consumers. The communications only and combined intervention stores (12 stores total) received in-store health communications, including taste tests, posters, and small refrigerators or freezers, to help stock and promote the sale of selected healthier foods. All customers of the participating corner stores were exposed to the 6-month intervention directed to that store. This study was approved by the Johns Hopkins Bloomberg School of Public Health Institutional Review Board.

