**BHRR study design.**

### Study hypotheses

The study tests the consumer-level hypotheses that, by the end of the 6-month intervention, customers of the 18 intervention stores (pricing only, communications only, and combined) will have, 1) greater increases in frequency of purchasing and consumption of the promoted foods than those at control stores, with the greatest increases among those consumers at combined intervention stores, and 2) greater increases in psychosocial factor scores relating to healthy food choices than those at control stores, with the greatest increases in the combined intervention stores. The study tests the store-level hypotheses that, by the end of the 6-month intervention, the 18 intervention storeowners will have 3) greater increases in sales and stocking of promoted foods compared to control stores, with the greatest increases in the combined intervention stores, and 4) greater increases in store owner psychosocial factor scores related to stocking and sales of promoted foods compared to control stores, with the greatest increases in the combined intervention stores.

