#### Primary outcomes

The primary outcomes of interest are the average change in consumer purchase of promoted foods and beverages, and related consumer psychosocial variables across treatment groups from baseline and post-intervention. The Adult Impact Questionnaire (AIQ) was used in past Baltimore Healthy Stores trials and was modified for this study [34,40,41]. Included in the 174-question AIQ is a section that assessed the frequency of food purchasing or ‘food getting’ (food obtained without purchasing) for 37 foods or food groups in the past 30 days, including promoted foods and unhealthier counterparts (e.g., baked chips vs. regular chips). The AIQ also contains sections that addressed individuals’ psychosocial factors, including self-efficacy, intentions, and knowledge to perform healthy eating behaviors. The self-efficacy section contained 10 questions that captured the respondents’ self-confidence in making healthy food choices. For example, respondents choose out of four responses ranging from “very easy” to “would be impossible” to questions such as, “How easy or difficult would it be for you to eat fresh or frozen vegetables every day?” The 10-question intentions section addressed respondents’ intentions to purchase, consume, and prepare foods promoted by the intervention using a forced-choice format (i.e., “The next time you buy a sweet snack, which will you choose, Donut, Granola Bar, or Tastykake?”), and the 10-question knowledge section tested the ability to answer nutrition-related questions, such as interpreting food labels.

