##### Sales of promoted foods

The SIQ captured promoted food sales by asking each participating store owner to estimate the number of units (i.e., cans, packages) of 15 key promoted foods sold in the store per day over the last 30 days. Additionally, a sales recall instrument, which has been used in earlier Baltimore-based studies, recorded store sales bi-monthly during the trial by asking each storeowner how many units of each promoted item were sold in the past 7 days [35]. A total of 12–15 weekly sales recalls were collected per store.

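### Hypotheses 1, 2 and 4 are set at the end of the intervention, but their outcomes were measured about 2 to 8 months after the discounts stopped, so a null result would be ambiguous

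*Protocol article*

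**What the plan says.** All references are to the protocol article.

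- **Time point of the hypotheses.** Study hypotheses frames the consumer hypotheses as changes seen "by the end of the 6-month intervention, customers of the 18 intervention stores" and uses the same time point for the store-level hypotheses. Hypotheses 1 and 2 concern consumer purchasing, consumption and psychosocial scores. Hypothesis 3 concerns store sales and stocking, and hypothesis 4 concerns storeowner psychosocial scores.
- **When the intervention ran.** Pricing intervention says the wholesale discounts were applied "from February to August 2013". Selection of foods for promotion gives the last stage as "Phase 3, from June to August 2013, promoted lower fat snack foods". Study design calls the whole a 6-month intervention.
- **When outcomes were measured.** Outcomes and measures states: "Post-intervention interviews were conducted from November 2013 to March 2014". This window covers storeowners and consumers together.
- **What is primary.** "The primary outcomes of interest are the average change in consumer purchase of promoted foods and beverages, and related consumer psychosocial variables". Food getting is asked "for 37 foods or food groups in the past 30 days".
- **Other time points.** Table 2 ticks every consumer impact measure at baseline and post-intervention only. Store stocking and store sales also have an interim tick.
- **In-trial sales data.** Under Sales of promoted foods: "A total of 12–15 weekly sales recalls were collected per store". Wholesaler sales of promoted foods describes wholesale records, by participating store, for January to September 2013.

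**The concern.** The theoretical framework rests the pricing arm on the law of demand: a lower price should raise purchases. That effect is expected while the lower price is in force. If the only consumer measurement comes months after the discount has gone, the contrast between randomised groups is a measure of persistence, not of the effect named in the hypotheses.

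The two quantities can differ. Purchases may rise under a discount and fall back once it ends. A null on food getting would then be compatible both with discounts that never worked and with discounts that worked while they lasted. The article says the trial will provide evidence on the effectiveness of price incentives, so the distinction bears on its main conclusion. An analysis plan cannot repair this, because the interviews have already been done.

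**Working it through.** **Inputs.** Discount period February to August 2013 (Pricing intervention). Last phase June to August 2013 (Selection of foods for promotion). Interviews November 2013 to March 2014 (Outcomes and measures), taken as 1 November 2013 to 31 March 2014. Recall of 30 days for food getting (Primary outcomes) and for the food frequency questionnaire (Secondary outcomes). The article gives months only, so the exact end date is an assumption and is varied.

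**The plan's own figure first.** At 30.44 days per month, 1 February to 1 August is 181 / 30.44 = 5.9 months, 15 February to 15 August is also 181 / 30.44 = 5.9, and 28 February to 31 August is 184 / 30.44 = 6.0. The stated 6 months is reproduced.

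**Gap from end of discounts to interview.** Gap = interview date minus end date. The recall window opens at interview date minus 30 days; for the earliest interview this is 1 November minus 30 days = 2 October 2013.

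| Assumed end of discounts | Gap, earliest interview | Gap, latest interview | Earliest recall window opens after the end by |
|---|---|---|---|
| 31 August 2013 | 62 days (2.0 months) | 212 days (7.0 months) | 62 − 30 = 32 days |
| 15 August 2013 | 78 days (2.6 months) | 228 days (7.5 months) | 78 − 30 = 48 days |
| 1 August 2013 | 92 days (3.0 months) | 242 days (8.0 months) | 92 − 30 = 62 days |

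**Overlap.** The smallest value in the last column is 32 days. On every reading, the overlap between a 30-day food recall and the discount period is 0 days.

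**Which outcomes are touched, and how.**

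- *Food getting (primary) and food frequency questionnaire (secondary):* delayed, and the recall window lies wholly after the discounts.
- *Consumer self-efficacy, intentions and knowledge (primary):* delayed. No 30-day recall is documented for these items, so the overlap calculation does not apply.
- *Storeowner psychosocial scores (hypothesis 4):* delayed in the same way.
- *Store sales and stocking (hypothesis 3):* the Store Impact Questionnaire is late, but sales recalls and environmental assessments were made during the trial and wholesale records cover it.

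**Search for a passage that resolves it.** The article does not say that discounts continued to the interviews, does not describe the hypotheses as sustained effects, and shows no consumer impact measure between baseline and post-intervention.

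**The case against.** The strongest reply is that the article calls these measurements post-intervention throughout. The primary outcome is change from baseline to post-intervention, the power section refers to a post-intervention sample, the Table 2 column carries that label, and the interview dates are openly stated. On this view only the wording of the hypotheses is loose, and a post-intervention difference between randomised groups is still a valid finding. That stands in part. The label is consistent and a positive result is evidence of effect. But it does not remove the conflict with the time point in the hypotheses, and it does not help with a null.

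Several stronger readings are tempting, and the documents do not support them.

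- *None of the hypotheses can be tested.* Hypothesis 3 has in-trial data, and the others can be tested as persisting effects.
- *No recall window overlaps any active communications.* Only the end of the discounts is explicit. The end of communications is inferred from Phase 3. Nothing says that posters, labels or refrigerators were removed, and storeowners were asked about displaying materials after the program.
- *The investigators would read a null as no effect.* The Analyses section gives no rule for reading a null, and the Discussion leaves open whether the price reduction reaches consumers.
- *The delay costs a known amount of power.* The power section states no power, standard deviation or intra-class correlation value, and ties its detectable differences to the post-intervention sample. Any figure would rest on assumed power and assumed persistence.

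**Conclusion.** The passages conflict, and hypotheses 1, 2 and 4 are wrong as written with respect to timing. Their outcomes were measured about 2 to 7 months after the discounts ended if the end was 31 August 2013, and about 3 to 8 months after if it was 1 August. For the primary food-getting outcome and the food frequency questionnaire, the recall has no overlap with the discount period under any end date in August. For the psychosocial scores the problem is the delay alone.

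The primary contrast therefore estimates an effect that persists after the discounts were withdrawn. For the communications factor, withdrawal is an inference, since materials or equipment may have stayed in stores. A positive result supports an effect. A null cannot tell no effect from one that faded.

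The conclusion assumes that the stated months bound the true dates and that the pooled interview window applies to consumers. It does not depend on any power figure.

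**What to change.** 1. Reconcile Study hypotheses with Selection of foods for promotion, Pricing intervention, Outcomes and measures, and Primary outcomes. Restate the hypotheses tested with the Adult Impact Questionnaire, the food frequency questionnaire and the storeowner psychosocial scales as effects about 2 to 8 months after the intervention ended, and give the actual end date. Alternatively, identify any consumer data collected at the end of the intervention.
2. State that a null on these outcomes does not show that the discounts had no effect while active.
3. Base the end-of-intervention sales claim in hypothesis 3 on the in-trial sales recalls, supported by the wholesale records, and not on the late Store Impact Questionnaire. Report how many recalls each store has in each phase: the article gives only a total per store, and 22 of the 24 storeowners completed the full intervention.
4. If time since the end is examined, use a treatment-by-time interaction as a sensitivity analysis. A main effect of weeks since August would adjust for level or season but would not estimate decay of the treatment effect.

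The cost is rewording and the use of data already planned or collected. No new data are needed. The price is a narrower consumer claim: the in-trial sales data do not rescue the consumer hypotheses.

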**Table 2 Tab2:** **Summary of study measures**

**Measures**	**Instrument**	**Baseline**	**Interim**	**Post-intervention**
**Impact**				
*Consumer-level*				
Food acquisition^1^	AIQ	✓		✓
Food-related psychosocial factors^1^	AIQ	✓		✓
Food source use	AIQ, 24-hour dietary recall	✓		✓
Health beliefs & attitudes	AIQ	✓		✓
Food Assistance participation	AIQ	✓		✓
Socio-demographics	AIQ	✓		✓
Household food security	AIQ	✓		✓
Weight	AIQ	✓		✓
Height	AIQ	✓		✓
Promoted food consumption^2^	QFFQ	✓		✓
Diet	24-hour dietary recall	✓		✓
*Store-level*				
Stock of promoted foods^2^	SIQ, Environmental Assessment	✓	✓	✓
Sales of promoted foods^2^	SIQ, Weekly sales recall	✓	✓	✓
Food-related psychosocial factors^2^	SIQ	✓		✓
Store operations	SIQ	✓		✓
Customer & employee attributes	SIQ	✓		✓
Food acquisition & promotion	SIQ	✓		✓
*Wholesale-level*				
Sales of promoted foods	Wholesale sales records	✓	✓	✓
**Process evaluation**				
Dose delivered, reach, fidelity of consumer communications (e.g., interactive sessions)	Interventionist PE form		✓	
Dose received of consumer communications and pricing components	Consumer intervention exposure form			✓
In-store communications strategies (store, wholesaler)	Environmental assessment, Wholesale PE form	✓	✓	✓
Healthy food availability & visibility (store, wholesaler)	Environmental assessment, Wholesaler PE form	✓	✓	✓
Price discount implementation (store, wholesaler)	Environmental assessment, Wholesale sales records	✓	✓	✓
Dose received of store owner communications and pricing components	Store intervention exposure form			✓
Small store environment & infrastructure	Environmental assessment	✓	✓	✓

^1^Primary outcome.

^2^Secondary outcome.

#### Primary outcomes

The primary outcomes of interest are the average change in consumer purchase of promoted foods and beverages, and related consumer psychosocial variables across treatment groups from baseline and post-intervention. The Adult Impact Questionnaire (AIQ) was used in past Baltimore Healthy Stores trials and was modified for this study [34,40,41]. Included in the 174-question AIQ is a section that assessed the frequency of food purchasing or ‘food getting’ (food obtained without purchasing) for 37 foods or food groups in the past 30 days, including promoted foods and unhealthier counterparts (e.g., baked chips vs. regular chips). The AIQ also contains sections that addressed individuals’ psychosocial factors, including self-efficacy, intentions, and knowledge to perform healthy eating behaviors. The self-efficacy section contained 10 questions that captured the respondents’ self-confidence in making healthy food choices. For example, respondents choose out of four responses ranging from “very easy” to “would be impossible” to questions such as, “How easy or difficult would it be for you to eat fresh or frozen vegetables every day?” The 10-question intentions section addressed respondents’ intentions to purchase, consume, and prepare foods promoted by the intervention using a forced-choice format (i.e., “The next time you buy a sweet snack, which will you choose, Donut, Granola Bar, or Tastykake?”), and the 10-question knowledge section tested the ability to answer nutrition-related questions, such as interpreting food labels.

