#### Consumer recruitment

A convenience sample of the first fifteen eligible customers/consumers that expressed interest in participating in the research study were recruited between May and September 2012 (total n = 360 consumers). Participants were eligible for the study if they: (1) were African American adults aged 21 or older, (2) lived within 0.25 miles of the store where they were recruited, (3) shopped in the store at least once a week, and (4) were the main food shopper for their household. All participants were interviewed outside of the stores where they were recruited, were explained the purpose of the study and signed a written informed consent form prior to interviews.

Both store owner and consumer respondents were compensated with $20 gift cards upon completion of each interview, which lasted approximately 1 hour.

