### Analyses

Descriptive statistics will be used to compare the demographic characteristics of intervention and control participants at baseline using means or medians for continuous variables and proportions for categorical variables. A series of scales and scores will be developed to evaluate the impact of the intervention on food acquisition and psychosocial factors for consumers and storeowners [35,40]. All scales will be assessed for internal consistency and reliability using Cronbach’s alpha.

Key outcome variables will be store- and consumer- level outcomes, with treatment condition as the primary exposure variable. An intent-to-treat approach will be used to test study hypotheses. Multiple regressions will be conducted to assess program impact on consumer food-getting and food consumption, consumer BMI and food security, consumer and storeowner psychosocial variables, and small store purchasing and sales. All analyses will account for clustering (by store for individual-level outcomes and over time for store-level outcomes) using multiple regressions with clustered robust standard errors (e.g. Huber-White), generalized estimating equations (GEE), or multilevel modeling methods [45]. We will first test for interactions between pricing and communications intervention groups, and will remove the interaction term if effects are not found [46]. Statistical tests will be two-tailed with an alpha set at 0.05. Summary statistics will be used as appropriate for process evaluation data.

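### The primary outcomes are framed as change from baseline and no baseline adjustment is stated; the models should adjust for the participant's own and the store-mean baseline score

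*Protocol article*

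**What the plan says.** The Primary outcomes section sets the scale of the outcome: "The primary outcomes of interest are the average change in consumer purchase of promoted foods and beverages". The related psychosocial variables are treated the same way, from baseline to post-intervention. The Study hypotheses section matches this. The first hypothesis predicts "greater increases in frequency of purchasing and consumption of the promoted foods than those at control stores", and the other three also compare increases with those in control stores.

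The Analyses section says "Multiple regressions will be conducted to assess program impact on consumer food-getting and food consumption", among other outcomes, "with treatment condition as the primary exposure variable". It names the test of the pricing-by-communications interaction and three options for clustering (cluster-robust standard errors, GEE or multilevel models). It names no covariates: a baseline score is neither included nor excluded.

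On timing, Consumer recruitment says the consumers "were recruited between May and September 2012". Outcomes and measures says "Baseline interviews were conducted with small storeowners and consumers from April to December 2012" and "Post-intervention interviews were conducted from November 2013 to March 2014".

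**The concern.** An outcome defined as average change, regressed on arm with no stated baseline term, is most naturally read as a comparison of raw change scores. The same contrast comes from a two-wave GEE or multilevel model with an arm-by-time term and free baseline means, given complete data. Either way the slope of follow-up on baseline is fixed at 1.

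Food getting is a self-reported 30-day frequency, and its two measurements are about one to two years apart. A slope near 1 is doubtful over such a gap. If the true slope is lower, subtracting the baseline adds noise. It also over-corrects any chance difference in baseline means between arms, and with 6 stores per arm such differences are to be expected. At stake are precision, and an arm contrast that moves with the baseline imbalance that happens to occur.

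**Working it through.** **The plan's own figures.** 12 consumers × 6 stores × 4 arms = 288 at follow-up; 15 × 24 = 360 at baseline, so 72 are expected to have baseline data only. The detectable differences in the Power calculation section (2, 5, 3 and about 20 points) cannot be reproduced, because no SD, ICC value, power or baseline–follow-up correlation is given. So one cannot tell whether they assume a change score.

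**Interval.** By consumer recruitment dates: September 2012 to November 2013 = 14 months; May 2012 to March 2014 = 22 months. By interview dates, which cover storeowners and consumers together: December 2012 to November 2013 = 11 months; April 2012 to March 2014 = 23 months.

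**Independent individuals.** Take equal SDs s at both times and correlation ρ (not in the documents; 0.3–0.7 assumed). Then Var(follow-up) = s², Var(change) = 2(1−ρ)s² and Var(ANCOVA) = (1−ρ²)s², so ANCOVA/change = (1+ρ)/2.

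| ρ | change / follow-up only | ANCOVA / follow-up only | ANCOVA / change |
|---|---|---|---|
| 0.3 | 1.40 | 0.91 | 0.65 |
| 0.5 | 1.00 | 0.75 | 0.75 |
| 0.7 | 0.60 | 0.51 | 0.85 |

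Below ρ = 0.5 a change score is noisier than ignoring baseline.

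**With clustering.** For store means of m = 12, with individual correlation ρ, store autocorrelation r and total variance 1: V = ICC + (1−ICC)/m, C = ICC·r + (1−ICC)·ρ/m, and R = C/V.

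- Change: 2(V−C).
- Store-mean adjustment: V(1−R²), so the ratio to change is (1+R)/2.
- One individual-level slope equal to ρ: V(1+ρ²) − 2ρC.

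The assumed ranges are ICC 0.01–0.10, ρ 0.3–0.7 and r 0.3–0.9.

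- Store-mean adjustment gives ratios of 0.65–0.91. The upper end is at ICC 0.10, ρ 0.7, r 0.9: V = 0.175, C = 0.1425, R = 0.814, ratio 0.907.
- A single individual-level slope gives 0.65–0.99. The upper end is at ICC 0.10, ρ 0.3, r 0.9: V = 0.175, C = 0.1125, so 0.704/0.714 = 0.986. Adding the store mean there brings the ratio to 0.82.

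**Dependence on imbalance.** Given a baseline difference d between arms and store-level slope R, the change contrast is shifted by −(1−R)d and the follow-up-only contrast by +Rd. A simulation of 24 stores × 12 (20,000 runs; ICC 0.05, ρ 0.5, r 0.6, all assumed) gave correlations between effect estimate and baseline imbalance of −0.48 for change, +0.54 for follow-up only and 0.00 for store-mean ANCOVA. The variance ratio ANCOVA/change was 0.81. The formula gives 0.77 for the same inputs; the difference is the price of estimating the slope from 24 stores.

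**Degrees of freedom.** Four arms and 24 stores leave 20; with a store-mean covariate, 19. The critical t goes from 2.086 to 2.093. For a contrast using two arms (12 stores), 10 becomes 9 and t goes from 2.228 to 2.262.

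**The case against.** The strongest reply is that the protocol article never says the change score will be analysed without adjustment. It is a condensed article, the analysis plan is not shown, and covariate lists are commonly left there. Calling treatment the primary exposure leaves room for other regressors. A change outcome is also compatible with baseline adjustment: if follow-up = a + τ·arm + β·baseline, then change = a + τ·arm + (β−1)·baseline, with the same τ. All of this stands. A reader might infer that the trial is committed to using baseline only by subtraction, and the document does not support that. But the possibility of adjustment shows only that the remedy fits the plan, not that the plan contains it. The outcome scale, by contrast, is stated.

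Three further objections hold in part.

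- **Bias.** Under randomisation the mean difference in change and in follow-up have the same expectation, so the change contrast is unbiased. The problem is its dependence on the imbalance that occurs. Stratification by WIC status and baseline unit sales of promoted foods may lessen imbalance in purchasing, but it does not use the consumers' own scores.
- **Season.** Recruitment ran mainly in the warm months and follow-up in the cold ones, which might suggest a seasonal bias. A shift common to all arms cancels from the contrast, and the stated baseline interview window runs to December.
- **Size.** The range rests on assumed correlations, and clustering can shrink the gain almost to nothing if only one individual-level slope is fitted.

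**Conclusion.** The point holds as one of efficiency and clarity. The protocol frames its primary outcomes as change and states no baseline adjustment; read as written, that fixes the baseline slope at 1 across a gap of 14–22 months (recruitment dates) or 11–23 months (interview dates). Under equal SDs and an assumed correlation of 0.3–0.7, adjustment cuts the variance to 0.65–0.85 of the change-score value for independent individuals. Allowing for clustering under the assumed ICCs and autocorrelations, the figure is about 0.65–0.91 with the store mean and up to 0.99 without it.

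Stronger statements are tempting but not supported. One could convert the ratios into a power loss: if ANCOVA had 80% power, Φ(2.80·√((1+ρ)/2) − 1.96) gives 62%, 68% and 73% for change scores at ρ = 0.3, 0.5 and 0.7. That ignores clustering and assumes both ρ and a reference power that the protocol does not state, so these are not this trial's figures. Nor does adjustment remove all chance imbalance. On average it removes the linear effect of imbalance in that outcome's own baseline, and nothing more.

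**What to change.** State in the Analyses section that each consumer-level primary model regresses the post-intervention score (or, with the same arm estimate, the change) on arm, with two covariates: the participant's own baseline score and the store-mean baseline. Apply the same own-baseline adjustment to the secondary outcomes and the storeowner scales. The outcome and hypothesis wording need not change.

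A mixed model with baseline means constrained equal across arms is an alternative. It also keeps the 72 participants expected to have baseline data only, and so is not strictly equivalent.

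The cost is a sentence or two and about one store-level degree of freedom. The baseline values are already collected. If adjustment is already intended, the edit merely records it.
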